## Abstract

**Background:**

It is well established that behavioral lifestyle interventions resulting in modest weight reduction in adults can prevent or delay type 2 diabetes mellitus; however in children, successful weight management interventions are rarely found outside of controlled clinical settings. The lack of effective community-based programs is a barrier to reducing obesity prevalence and diabetes risk in children. The objective of our study is to develop and test a group-randomized family-centered community-based type 2 diabetes prevention intervention targeting at-risk children, 9- to 12-years-old.

**Methods/Design:**

Using participatory methods, the adult-focused YMCA Diabetes Prevention Program was adapted for families, creating a novel lifestyle behavior change program focused on healthy eating, physical activity, and a supportive home environment. The program will be tested in sixty 9- to 12-year-old children at risk of diabetes and sixty parents over 12 consecutive weeks with two intervention formats randomized by location: a face-to-face instructor-led program, or a hybrid program with alternating face-to-face and mobile technology-delivered content. Anthropometric, behavioral, psychosocial and physiological outcomes will be assessed at baseline, post-intervention (12 weeks), and follow-up (24 weeks). Secondary outcomes are participant acceptability, feasibility, and adherence. The RE-AIM framework (reach, efficacy, adoption, implementation, and maintenance) will guide intervention implementation and evaluation. Changes at 12 weeks will be assessed using a paired t-test combining both delivery formats. Exploratory models using linear regression analysis will estimate the magnitude of the difference between the face-to-face and hybrid format. The sample size of 60 children, informed by a previous YMCA intervention in which −4.3 % change in overweight (SE = 1.1) was observed over 6 months, will give us 80 % power to detect an effect size of this magnitude, assuming a one-sided test at alpha = 0.05.

**Discussion:**

The proposed study capitalizes on a partnership with the YMCA, a popular and widespread community organization, and uses mobile technologies to extend program reach while potentially reducing burden associated with weekly attendance. The long-term goal is to create a scalable, replicable, and sustainable pediatric “diabesity” prevention program that overcomes existing barriers to the translation of efficacious interventions into effective community programs.

**Trial registration:**

ClinicalTrials.gov, NCT02421198 on April 15, 2015

## Background

The statistics are startling: nearly one-third of U.S. children and adolescents are overweight and one in five are obese [1]. Given the strong association between obesity in youth and the risk for chronic disease, and persistence of obesity into adulthood [2, 3], weight control and obesity prevention are critical to type 2 diabetes mellitus (T2D) and cardiovascular disease prevention. In children, short-term weight loss/weight management success has been achieved in controlled clinical and research settings [4, 5]; however, long-term success is rare, adherence is low, and studies outside of these settings often lack comparison groups and clinical outcomes other than body weight and body mass index (BMI) [6]. The paucity of effective obesity prevention programs adapted for community settings represents a significant barrier to reducing obesity prevalence and T2D risk in children.

In adults, behavioral interventions have proved more efficacious than pharmacological interventions for T2D prevention [7] with established evidence for long-term risk reduction [8, 9]. In youth, novel strategies for increasing engagement and supporting parental involvement are needed to achieve similar effects. Studies suggest that effective youth interventions are family-centered [10, 11], target both diet and physical activity [5, 12], and include activities that promote adoption of healthy behaviors by parents who are often also at high risk for T2D [13]. Parents shape their child’s food and physical activity environments, making them central agents for prevention and treatment of weight-related problems. In this role, parents require a combination of information, skills, resources, and opportunities to support their child in healthy behavior change [14, 15].

The proposed program - EPIC Kids (Encourage - Practice - Inspire - Change) will provide critical infrastructure to support youth and families in making lifestyle changes by adapting the successful adult YMCA Diabetes Prevention Program (YDPP) [7, 16] for at-risk (≥85 BMI percentile) children, ages 9- to 12-years-old, and their families. Our goal is to promote youth and family adoption of behaviors associated with a healthy weight trajectory to prevent excess weight gain while supporting normal growth and development in children. Target lifestyle behaviors in support of this goal are to make physical activity an integral and routine part of life, eat a healthy diet (both quality and quantity) and create food and physical activity environments to insure healthy options and behaviors are the routine, easy choice.

The EPIC Kids Study has the following objectives:Adapt the efficacious Diabetes Prevention Program (DPP) in adults – the adult YMCA DPP – for delivery to children, ages 9-12-years-old, and their familiesTest the impact of the program on child anthropometric, behavioral, physiological, and psychosocial outcomesAssess feasibility, participant acceptance (child and parent), and retention rates of the program using two delivery formats randomized by YMCA location: a 12-week face-to-face program and a 12-week hybrid face-to-face and mobile device-based program

Herein we describe the design and evaluation of the EPIC Kids Study, a family-focused, YMCA-based diabetes prevention program specifically designed for at-risk children and their families.

## Methods/Design

### Study design

The impact of the EPIC Kids intervention will be evaluated using a group-randomized, non-inferiority trial design with three data collection points: baseline, post-intervention (immediately post program completion at 12 weeks), and follow-up (24 weeks) (Fig. 1). The program will be tested with sixty, 9- to 12 year-old children and their parent(s) or primary caregiver(s) at two YMCA locations in Tucson, Arizona where families lack services and resources needed for T2D prevention. Randomization to delivery formats will occur by YMCA location to minimize between-group contacts. One site will conduct a face-to-face weekly YMCA lifestyle coach-led program, while the second site will host a program equivalent in duration, frequency, and content, also lead by YMCA coaches, but with 5 weeks (40 %) of content digitally delivered using study-provided mobile devices (Kindle Fire HDX7, Amazon). Thirty families will be recruited to participate in each intervention format; each family will be assigned to an intervention group led by two trained YMCA lifestyle coaches and consisting of up to 9 other families. Weekly sessions will occur over 1.5 h for 12 weeks.

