### Sample size and power

The primary outcome is change in percent overweight. Our estimated sample size was informed by the results of Foster et al. [18] who observed a mean decrease of 4.3 % in percentage overweight (SE = 1.1) in a YMCA-based pediatric obesity intervention over 6 months, and is based on the number of participants needed to detect an effect size of this magnitude with 80 % power assuming a one-sided test at alpha = 0.05. Given a final sample of 48 children and allowing for up to 20 % attrition, 60 participants will be recruited.

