### Statistical analysis

Outcome measures will be stratified by delivery format to assess whether the mobile technology-supported delivery of the intervention is as efficacious as the face-to-face format. Descriptive statistics for change in endpoints (mean, median, and standard deviation) between baseline and 12-week measurements will be computed separately for each program format (face-to-face or hybrid mobile technology-supported program). The statistical significance of the change at 12 weeks will be assessed using a paired t-test combining both formats. One-sided statistical tests will be used, as the interventions approaches are of interest only if they decrease the percentage overweight and lead to improvements in diabetes risk factors. Statistical significance is set at alpha = 0.05. Sample size constraints do not allow adequate statistical power to formally test for differences between the two formats. However, exploratory models using linear regression analysis will estimate the magnitude of the difference between the face-to-face and combined formats, adjusted for baseline levels and the potential correlation between the participants within a given YMCA (expected to be small). These parameter estimates will provide effect sizes to appropriately power a larger study comparing the two formats. Since this is a randomized comparison, confounding is not an issue as long as there is non-differential dropout between the two formats. Differential dropout between the two formats will be assessed using a Fisher’s Exact Test. Similar analyses will assess whether improvements are maintained after the intervention ends, by comparing the 24-week versus 12-week values. We acknowledge the potential for differential loss to follow-up and missing data. Baseline values of those who complete the study versus those who do not will be compared using two sample independent t tests and Fisher’s Exact Tests, as appropriate. Additional sensitivity analyses will use multiple imputation for missing values and an intent-to-treat analysis with baseline values carried forward.

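### The study is labelled a non-inferiority trial, but its sample size, its only efficacy test and its stated power limits cannot support a non-inferiority conclusion

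*Protocol article*

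**What the plan says.** Under Study design, the article states: "The impact of the EPIC Kids intervention will be evaluated using a group-randomized, non-inferiority trial design with three data collection points". Two YMCA sites are randomized, one to each format, with thirty families per format.

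Under Statistical analysis, outcomes are to be stratified by format "to assess whether the mobile technology-supported delivery of the intervention is as efficacious as the face-to-face format".

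The sizing and testing are set elsewhere:

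- **Sample size and power:** "The primary outcome is change in percent overweight". The number is chosen to detect a mean decrease of 4.3 points (SE 1.1, taken from an earlier YMCA-based paediatric programme over 6 months) with "80 % power assuming a one-sided test at alpha = 0.05". This gives 48 evaluable children and 60 recruited.
- **Statistical analysis, efficacy test:** the 12-week change is tested by a paired t-test that combines both formats.
- **Statistical analysis, format comparison:** "Sample size constraints do not allow adequate statistical power to formally test for differences between the two formats". Exploratory linear regression will estimate the difference, and the estimates will be used to size a larger study.

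The article states no non-inferiority margin.

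**The concern.** A non-inferiority design makes a specific promise: the trial can rule out a loss of effect larger than a stated margin. That requires a between-format hypothesis, a margin, a decision rule and a sample size matched to them. Here the label and the equal-efficacy aim make the promise, while the sizing and the test serve a pooled pre-post question. Pooling the formats removes the very contrast that non-inferiority concerns.

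The missing margin alone could be put down to a condensed article. The contradiction cannot, because the article itself fixes the sizing and the efficacy test on a different hypothesis. A margin in an unseen analysis plan would not make this sample or this test suitable.

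At stake is how the results may be read. Under a non-inferiority label, two similar mean changes, or a wide and non-significant difference, can easily be taken as evidence that hybrid delivery loses nothing.

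**Working it through.** **1. The plan's own figures.** Inputs from Sample size and power: effect 4.3, one-sided alpha 0.05, power 80%, 48 evaluable, 20% attrition.

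- Attrition: 48 / (1 − 0.20) = 60. This reproduces exactly.
- The 48: for a single mean change, n = (SD × (1.645 + 0.842) / 4.3)². The article gives no SD. The SE of 1.1 converts to an SD only with the source study's sample size, which is not stated. Solving for the SD: 4.3 × √48 / 2.487 ≈ 12.0 (about 11.8 with the t distribution). So 48 is neither confirmed nor shown to be wrong; it implies an SD of change near 12.

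**2. What the same children could show on non-inferiority.** Assumptions: 24 analysed per format (30 less 20%), true difference zero, one-sided alpha 0.05, no clustering, normal approximation. The SD is assumed.

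SE of the difference = SD × √(2/24). Margin with 80% power = 2.487 × SE.

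| SD of change | SE of difference | Margin with 80% power |
|---|---|---|
| 6 | 1.73 | 4.3 |
| 7.62 (if the source n were 48) | 2.20 | 5.5 |
| 12 (implied by n = 48) | 3.46 | 8.6 |

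The last row does not depend on knowing the SD, if 48 was sized as the article says. Because √(2/24) = 2/√48, a sample with 80% power for a pooled change of 4.3 has 80% power only for a between-format margin of 2 × 4.3 = 8.6.

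**3. Reading the margins.** If face-to-face delivery achieved the planned 4.3-point decrease, a margin of 4.3 or more would admit a hybrid format with no effect at all. With the margin set at 4.3, power (noncentral t) is 78.8% at SD 6 and 33.7% at SD 12.

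**4. One site per format.** The interval from a regression on children cannot include variation between sites, because each format has a single site. With an assumed intraclass correlation (ICC), the true SE is √(2 × SD² × (ICC + (1 − ICC)/24)). At SD 11.98 this is 3.84 for an ICC of 0.01 and 5.07 for 0.05, against 3.46 when clustering is ignored. The margins in step 2 are therefore optimistic. More children at the same two sites would not separate format from site.

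**The case against.** The strongest reply is that the article is already candid. Statistical analysis calls the format models exploratory, says the study lacks power for a formal comparison, and gives the estimates' use as planning a larger study. The objectives contain no non-inferiority hypothesis; the objective on formats concerns feasibility, acceptance and retention. All of this stands. It means that the label and one aim sentence are at fault, not the analysis.

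Several stronger readings are tempting but are not supported:

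- **That the investigators will report non-inferiority.** Nothing in the article plans that conclusion or gives a rule for it. Anticipated results states only an expectation of comparable outcomes.
- **That every margin with 80% power is at least the whole planned effect.** This holds only for an SD of about 6 or more. At SD 4 the margin would be 2.487 × 4 × √(2/24) ≈ 2.9. No SD is stated.
- **That no proven effect exists from which to derive a margin.** The adapted programme is itself under test and there is no untreated arm, so the question is open. But the article cites a 4.3-point decrease in a YMCA paediatric programme, and whether that source could support a margin cannot be judged from the article.
- **That the uncontrolled pooled test adds to this point.** What a pre-post change can prove is a separate matter and carries no weight here.

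**Conclusion.** The point holds as an internal contradiction: a non-inferiority label and an equal-efficacy aim sit on a study that is sized and tested for a pooled change and, by its own statement, cannot formally compare the formats. The design cannot support a non-inferiority conclusion.

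That conclusion comes from the text and needs no assumed figure. The numbers only illustrate its size: a margin with 80% power of about 4.3 points at SD 6 and 8.6 at SD 12, against 4.3 points planned for the whole programme. They rest on 24 children per format, zero true difference, one-sided alpha 0.05, no clustering and an assumed SD, of which only the value near 12 is tied to the plan's own sample size.

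This should be fixed, but it does not invalidate the study. The sample size and the pooled test do not depend on the label.

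**What to change.** - **Study design:** replace the non-inferiority wording with *pilot pre-post study at two sites randomized to delivery format, with an exploratory comparison of formats*. This keeps the true fact that sites were randomized.
- **Statistical analysis:** replace the equal-efficacy aim with estimation of hybrid minus face-to-face, reported with a 95% confidence interval. State that, with one site per format, the interval omits between-site variation and cannot separate format from site. The regression sentence should name this contrast; it now sets face-to-face against the combined formats, whereas the abstract names hybrid.
- **Claims:** state that no non-inferiority or equivalence claim will be made.

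The cost is a few sentences and a weaker design label. Recruitment, visits, measurements and the pooled test are unchanged. The registry record was not available, so no change to it is asked for here.

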**Fig. 1 Fig1:**
[figure not shown]
EPIC Kids Study design, recruitment, procedures

Baseline, post-intervention (12 weeks), and follow-up (24 weeks) measures will assess changes in child anthropometric, behavioral, psychosocial, and physiological outcomes. We will also determine whether the two delivery formats are acceptable and feasible, and if the use of technology reduces participant burden and improves adherence for the ‘hybrid’ condition. The study protocol was approved by the University of Arizona Institutional Review Board, and is registered with ClinicalTrials.gov (NCT02421198).

### Participants

Eligible participants are 9 to 12-years-old at study enrollment, have a BMI at or greater than the 85th percentile for age and sex, and have one or more of the following T2D risk factors: ethnic minority, first or second degree relative with T2D, conditions associated with insulin resistance or metabolic syndrome (including acanthosis nigricans, hypertension, dyslipidemia, polycystic ovarian disease, small for gestational age birth weight, maternal history of gestational diabetes [17]). Eligible children must also have a primary caregiver willing to participate in intervention sessions and activities (note: primary caregiver is an adult who most frequently prepares/obtains food, regulates media use, and provides physical activity opportunities for the child), be willing to use a study-provided mobile device throughout intervention, and speak and read English. Exclusion criteria are previously diagnosed Type 1 or Type 2 diabetes mellitus (this is not an exclusion criteria for the caregiver), psychiatric disturbances or mental illness, limitations preventing physical activity, or using medications known to cause weight loss or gain or affect appetite.

Participants will be recruited through pediatric and family medicine practices, the Southern Arizona YMCA membership, and the Tucson community (e.g., libraries, community centers, public health department, and local health fairs) using electronic announcements, flyers, posters, and word-of-mouth between May and August 2015, and between October 2015 and January 2016. Respondents will be invited to attend study information sessions held at participating YMCA locations where eligibility will be confirmed. Interested and eligible respondents will complete the informed consent process following University of Arizona Institutional Review Board-approved materials and methods and assigned a study location based on geographical proximity. Written consent will be obtained from parents; verbal assent will be obtained from youth and documented in writing by study staff. Families who are not yet YMCA members will be provided access to YMCA facilities free of charge for the duration of the study, with an opportunity to continue at a reduced rate after the study has concluded.

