Physiological outcomes will be assessed through 12-hour fasting insulin, glucose, and lipids drawn at J2 Laboratories, Tucson, Arizona, by a trained phlebotomist and placed into serum separator vacuum tubes. Insulin resistance (IR) will be assessed using HOMA [46], shown to more sensitive for identifying youth with metabolic dysregulation than an impaired fasting glucose threshold [47]. Calculation of IR is based on modeling of fasting insulin and glucose concentrations using the formula: fasting insulin (μU/ml) × fasting glucose (mmol/L)/22.5 = HOMA. HOMA correlates closely to IR as measured by euglycemic clamp [48], and a HOMA insulin resistance value of 2.6 will be used as the upper limit of normal [49]. Blood pressure will be measured on the non-dominant arm using an automatic monitor (Omron HBP-1300, Hoofddorp, The Netherlands) and cuff-sizes appropriate for the mid-upper arm circumference. Systolic and diastolic blood pressure will be measured two times with 5 min intervals while the participant is seated and resting. The definition of hypertension will be adjusted for age per national guidelines [50]. Individuals with fasting glucose values >126 mg/dL and no previous history of T2D will be referred to their primary care provider. The study medical director will be immediately informed and arrange appropriate follow-up depending on the level of blood glucose elevation and symptoms. Maturity will be assessed using Tanner’s validated self-report questionnaire which presents illustrations of developmental stages shown to agree with pubertal staging by a physician [51, 52].

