	Baseline questionnaire	• Participant demographics • New or past YMCA members • Motivation to join • Willingness to participate (distance to travel) • Competing programs	Enrollment
Efficacy	Lifestyle coach training survey & focus group	• Prior experience as a Lifestyle/DPP^a^ Coach • Comprehension of material • Knowledge and skills acquired • Self-efficacy/preparedness • Perceived barriers/ potential solutions • Motivation to lead • Acceptability (likes/ dislikes)	Pre-study training (1 time)
	Telephone debriefing with lifestyle coaches	• Ease of implementation • Barriers/potential solutions • Perceived participation • Time management	After first lesson (1 time)
	Lifestyle coach weekly survey	• Curriculum comprehension • Ease of implementation • Fidelity of lesson (delivered as written & on time) • Perceived self-efficacy • Motivation to lead again • Perceived participant participation • Perceived barriers/solutions • Acceptability (likes/dislikes)	Weekly after each lesson (11 times)
	Attendance record	• Adherence (in-person) • Mobile data analytics (adherence for mobile-device delivered group)	Weekly (12 times)
	Participant weekly questionnaire (Child, parent)	• Comprehension • New knowledge • Usefulness • Motivation • Likelihood to adopt (short & long-term) • Enjoyment • Acceptability (likes/dislikes) • Suggestions for improvement	Weekly after each lesson (11 times)
	UA staff observation rubric	• Study fidelity (delivered as written and on time) • Participant engagement (quantity & quality) • Instructor communication/organization • Instructor classroom management • Instructor support of student needs	4x each study site
	Lifestyle coaches final survey	• Perceived efficacy of intervention • Desire to continue program • Average preparation time • Time substitution (substituted activity if not involved in the intervention delivery) • Enjoyment & acceptability (likes/dislikes)	End of program (1 time)
	Participant final survey (Child and parent)	• Perceived effectiveness of instructor • Adoption of lifestyle changes due to program • Perceived long-term maintenance of changes • Likelihood to recommend program & perceived effectiveness of intervention for others • Use of YMCA for other purposes • Likelihood of future YMCA use • Cost of physical activity or food items due to intervention^b^ • Time substitution (activity substituted if they were not in the intervention)^b^	End of program (1 time)

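### Children referred to care for a high baseline glucose stay in the uncontrolled one-sided glucose and HOMA tests, so care begun after baseline could be counted as programme effect

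*Protocol article*

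**What the plan says.** **Who enters.** The Participants section excludes previously diagnosed type 1 or type 2 diabetes, and children "using medications known to cause weight loss or gain or affect appetite". A glucose value found at the baseline blood draw is not an exclusion.

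**What happens after a high value.** The first Data collection section, under physiological outcomes, says: "Individuals with fasting glucose values >126 mg/dL and no previous history of T2D will be referred to their primary care provider". The study medical director is informed at once and arranges follow-up. The same section makes fasting insulin, glucose, lipids, HOMA and blood pressure trial outcomes, measured at baseline, 12 and 24 weeks.

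**How change is tested.** The Statistical analysis section says: "The statistical significance of the change at 12 weeks will be assessed using a paired t-test combining both formats". The tests are one-sided at 0.05, because the approaches are of interest "only if they decrease the percentage overweight and lead to improvements in diabetes risk factors". Both formats are active. The stated sensitivity analyses (multiple imputation, baseline carried forward) deal with missing values only.

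**What is asked about other help.** In Table 3 the baseline questionnaire, given at enrollment, lists "Willingness to participate (distance to travel) • Competing programs". No later row repeats the competing-programme item.

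**The concern.** A paired test without an untreated group credits everything that changed between visits to the programme. For glucose and HOMA, the trial itself can set off one such change: its baseline test finds a high value, the child is referred, and the same child's later value enters the test of improvement. The children concerned have the highest baseline values and so the most room to fall. In a sample of about 48, a few large falls can move the result.

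Drug changes between visits, and programmes joined after enrollment, act in the same way on lipids, blood pressure and, less so, percent overweight. The Statistical analysis section sets confounding aside because the comparison is randomized. That argument concerns face-to-face against hybrid delivery and does not protect the pooled pre-post test. At stake is whether an improvement in diabetes risk factors can be attributed to EPIC Kids.

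**Working it through.** **1. The plan's own figure.** 48 / (1 - 0.20) = 60 children recruited, as stated. The checks below use the 48 expected to finish.

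**2. Does a referred child stay in the analysis?** Three statements, side by side: only a previous diagnosis excludes (Participants); a child with no such history and a value above 126 mg/dL is referred (Data collection); change is tested on all paired values, both formats together (Statistical analysis). No statement takes the referred child out, so on the text the child stays.

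**3. Glucose.** The documents give neither the number of referred children, nor their fall, nor the SD of change. Assumed: SD of change 6, 8 or 10 mg/dL; m of 48 children fall by a further F = 30 or 60 mg/dL; no programme effect. The shift in the mean is m x F / 48. The test is a one-sided paired t-test with critical value 1.678 on 47 degrees of freedom, with 100,000 simulated trials per setting.

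| m | F (mg/dL) | Mean shift (mg/dL) | Chance of significance |
|---|---|---|---|
| 0 | - | 0 | 5% |
| 1 | 30 | 0.63 | about 9% |
| 1 | 60 | 1.25 | 7-10% |
| 2 | 30 | 1.25 | 14-18% |
| 2 | 60 | 2.50 | 19-20% |
| 3 | 30 | 1.88 | 22-32% |
| 3 | 60 | 3.75 | 36-46% |

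The ranges cover the three SDs. A larger fall does not always raise the chance, because it inflates the SD as well as moving the mean. The upper end needs baselines well above the referral value: a child just above 126 who fell by 60 would end near 66.

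HOMA is insulin x glucose / 22.5, so at unchanged insulin it falls in proportion to glucose. The direction is the same; the size for HOMA was not simulated.

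**4. Primary outcome, for scale.** For n = 48, one-sided 0.05 and 80% power, the noncentral t gives a standardized change of 0.364. The implied SD is 4.3 / 0.364 = 11.8 points and the SE is 11.8 / sqrt(48) = 1.70. Assume that a share p of children has a co-intervention worth E further points, and no programme effect. The mean shift is p x E and the variance is SD^2 + p(1 - p)E^2.
- p = 10%, E = 5: shift 0.5 (0.5 / 4.3 = 12%), chance of significance about 9%.
- p = 10%, E = 10: shift 1.0 (23%), about 14%.
- p = 20%, E = 10: shift 2.0 (47%), about 29%.

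Again, p and E are assumptions.

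**5. Would dropping children solve it?** That depends on when the reason for dropping arises.
- *After baseline.* Suppose that starting a drug or programme is correlated 0.5 with worsening (assumed) and that there is no programme effect. Dropping the 10% who start raises the chance of significance from 5% to about 16%; dropping 20% raises it to about 30%. The remedy would then bias toward success.
- *At baseline.* Removing children above the referral value cuts off the top of the baseline distribution. Regression to the mean then pushes the remaining children's expected change slightly upward, against an improvement.

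**The case against.** The case on the other side is strong on several points.

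- **The exclusion list is not the defect.** A reader might infer that it should have covered blood pressure, lipid and glucose drugs. A child on a stable drug contributes no drug-induced change to a paired difference, and no entry criterion can prevent a drug started later. For percent overweight, the list already covers the most relevant drugs at entry. This stands.
- **The criteria do not select children with hypertension, dyslipidemia or polycystic ovarian disease.** A child must "have one or more of the following T2D risk factors: ethnic minority, first or second degree relative with T2D", or one of the listed conditions. Any one is enough, so those conditions are admitted but not required. This stands.
- **Free YMCA access is not an outside co-intervention.** The study supplies it to all participants. The final survey in Table 3 also asks about use of the YMCA for other purposes, so such activity is not unseen at the end of the programme. This stands; what is left is programmes outside the YMCA, and the 24-week visit.
- **This is a condensed article.** A medication log may sit in the full protocol or analysis plan, so its absence here is not counted as an error. What is held against the text is what it does state: the referral, the diabetes exclusion, the pooled one-sided test, and a competing-programme item timed at enrollment when other Table 3 rows give repeat times.
- **The counts and falls are assumed, and referral is not the same as treatment.** True. With no referred child there is no effect through this route; with one, the error rate is 7-10%.
- **Growth, season and regression to the mean are just as inseparable from the programme.** Also true. Co-treatment differs in that the trial's own test can start it and the affected children can be identified at baseline.

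**Conclusion.** The concern holds in a limited form. On the text, children referred for a high baseline glucose remain in one-sided, uncontrolled glucose and HOMA tests, and care begun after referral could be counted as programme effect. Other drug changes or programmes begun between visits could act likewise on the other outcomes, chiefly the secondary physiological ones.

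The size depends on a number that the documents do not give. Under the assumed SDs and falls, the false-positive rate for glucose is about 7-10% with one affected child among 48, 14-20% with two and 22-46% with three. With none it stays at 5%. The figures for percent overweight only show scale. The documents do not support saying that the bias will occur, or that the primary result is compromised. The point justifies a cheap improvement to the secondary analyses, with no change to design, sample size or care.

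**What to change.** 1. In Statistical analysis, add glucose and HOMA change analyses without children whose baseline glucose is above the trial's own referral value, shown beside the all-children result. Do not attribute a glucose or HOMA improvement to the programme if it depends on those children.
2. Repeat the Table 3 competing-programme item, and add one question on medication changes, on the questionnaires already given at 12 and 24 weeks. Report the counts.
3. Treat any analysis that drops children for a drug or programme change after baseline as descriptive only, because it selects on post-baseline events.

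The cost is two questionnaire items and perhaps a few children fewer in one analysis. Eligibility, referral and clinical follow-up stay as they are.
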